### Personalized dosimetry

The in vivo biodistribution of [^131^I]ICF01012 will be assessed using planar whole body (2D) and thorax-abdomen-pelvis SPECT-CT acquisitions (3D). Planar and SPECT acquisitions will be performed following the Medical Internal Radiation Dose Committee (MIRD) guidelines for quantitative imaging with ^131^I [28, 29] on a Symbia Intevo T6 SPECT/CT (Siemens), equipped with HEGP collimators and 3/8″ NaI detector crystals. The time-integrated activity $$\overset{\sim }{A}\left({r}_S\right)$$ (or total number of nuclear transformations in source region *r*_*S*_) will be calculated by fitting time-activity curves for each region previously segmented on CT scan. The time-integrated activity obtained for diagnostic part is then scaled with the expected injected activity for therapeutic part. The patient specific S-values (defined as absorbed dose in target region *r*_*T*_ per nuclear transformation in source region *r*_*S*_) will be computed by Monte-Carlo simulation using GATE. The mean absorbed dose to organs and tumours will be calculated using MIRD formalism [21]. According to this formalism, the mean absorbed dose is given by:$$D\left({r}_T\right)=\sum_{r_S}\overset{\sim }{A}\left({r}_S\right)S\left({r}_T\leftarrow {r}_S\right)$$

The most unfavourable result of the dosimetry based on 2D or 3D imaging quantification will be retained.

### Statistical considerations

#### Sample size

Using a CRM model with 4 dose levels, i.e. with cohorts of one patient by dose level and at least 6 patients at the recommended dose, a minimum of 6 patients and a maximum of 18 patients should be included in the “therapeutic part”. Sample size calculation for the selection part is based on the hypothesis that 50% of patients will have at least an [^131^I]ICF01012 lesion uptake as observed with BZA2 in phase III study [8] and thus be eligible for the therapeutic part. Therefore, between 12 to 36 patients will be enrolled in the selection part in order to ensure the necessary sample size for the therapeutic part (between 6 to 18).

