## Methods/design

### Study design

This is an open-label, multicentric, “first-in-human”, dose-escalation phase I trial of a radiopharmaceutical.

The study based on a theranostic approach is divided in 2 steps:Firstly, a “selection part”, to determine if the patient is eligible for therapy, i.e., if the radiopharmaceutical is up-taken by metastases. During this phase, a single IV injection of low activity of [^131^I]ICF01012, called “diagnostic dose” will be injected to the patient. Pre-treatment dosimetry allows to measure for each patient the absorbed dose by organs and tissues. Patients will be eligible for the second step, the “therapeutic part” if they present at least one tumor lesion with [^131^I]ICF01012 uptake and if mean absorbed dose (AD) to liver < 26 Gy, kidney AD < 16.2 Gy, lung AD < 15 Gy et retina AD < 40 Gy.Secondly, a “therapeutic part” consisting of a single IV injection of [^131^I]ICF01012 at a therapeutic activity. The dose escalation will be driven by a Continual Reassessment Method (CRM) [27] with 4 [^131^I]ICF01012 activity levels: 800, 1600, 2700, or 4000 MBq/m^2^.

The duration of intervention for each patient will be 7 days (diagnostic phase only) or 3 weeks (diagnostic phase + therapeutic phase). Follow-up will last 4 weeks (diagnostic phase only) or 10 weeks (diagnostic phase + therapeutic phase).

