##### Selection part

For the selection part, patients will be able to stay hospitalized for 24 h after injection at their request. The diagnostic dose will be injected at D0 with a follow-up of vital signs: before, 5 min after the start of infusion, at the end of infusion, 30 min, 1 h, 3 h, and 24 h (D1) after end of infusion and then at D4 and D7.

The in vivo biodistribution of [^131^I]ICF01012 will be assessed using whole-body planar scintigraphy acquisition (30 min, 1 h, 3 h at D0, 24 h (at D1) 4 days (D4) and 7 days (D7) after injection) and Single Photon Emission Computed Tomography/Computed Tomography (SPECT-CT) acquisitions at 3 h (D0), 24 h (D1), 4 days after injection (D4) and SPECT at D7.

Blood samples for pharmacokinetic study will be collected at 5, 10, 15, 30 min, 1 h, 3 h (D0) 24 h (D1), 96 h (D4) and 168 h (D7) post-injection. A 24-h urine collection will be realized for hospitalized patients for excretion evaluation. Blood and urine tests for safety evaluation will be performed at D4 and D7.

The eligibility criteria for therapeutic part (at least one metastasis with [^131^I]ICF01012 uptake and an acceptable AD to major healthy organs) will be checked from D4 until D7 with dosimetry results. After verification of the eligibity criteria for therapeutic part, a dose allocation request will be done using an eCRF. Eligible patients for therapeutic phase will have an ocular optical coherence tomography (OCT) before therapeutic injection.

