## Discussion

The MELRIV-1 trial is the first in human evaluation of the [^131^I]ICF01012 TRT in metastatic malignant melanomas. This study aims to determine the recommended dose of [^131^I]ICF01012 to administer for the treatment of patients with pigmented metastatic melanoma (binding [^131^I]ICF01012).

[^131^I]ICF01012 is a melanin-targeting compound allowing both imaging and TRT [18]. Even though targeting melanin to destroy melanoma cells is a seducing approach, some concerns exist and have been taken in account for this study design. Firstly, melanoma cells can lose the ability to synthesize melanin during the dedifferentiation process [30]. BZA2 phase 3 studies showed that approximately 50% of metastatic lesions did not capture melanin radiotracer [17]. Secondly, melanin is also present in healthy organs and tissues, as skin (keratinocytes, nævi), eyes (retinal pigment epithelium), brain (basal ganglia), heart, and adipose tissues (morbid obesity) [31]. Moreover, classically, radiation sensitive organs in TRT are red bone marrow, kidneys and liver. A radiosensitivity inter-patient variation of 20% dose can exist [32].

The design chosen in this trial was based on a theranostic approach with a pre-treatment dosimetry, with an infra-therapeutic dose of the [^131^I]ICF01012 that permits to select the patients who may benefit of a therapeutic dose of [^131^I]ICF01012, with at least one tumour lesion with [^131^I]ICF01012 uptake and an acceptable AD to healthy organ. Radiotoxicity must be minimized with a pre-treatment dosimetry. A precise dosimetry, i.e. the quantification of energy deposed in tumour and non-target organs, is the main concern for TRT evaluation in a clinical trial [21, 23].

The used of radiolabelled benzamides may constitute a therapeutic solution for melanomas resistant to therapy (for review see [10]). Compared to external radiation beam therapy, TRT allows a systemic treatment of a polymetastatic disease. [^131^I]ICF01012 is an original strategy for targeting pigmented lesions, but also unpigmented metastases through a potential abscopal effect [25].

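### Thirty-six selection patients do not ensure 18 treated: the calculation counts uptake alone as eligibility and plans to the expected value with no margin

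*Protocol article*

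**What the plan says.** All places are in the protocol article.

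- **Sample size.** For the therapeutic part, "a minimum of 6 patients and a maximum of 18 patients should be included". The selection part is "based on the hypothesis that 50% of patients will have at least an" avid lesion, a rate attributed to the BZA2 phase III study and cited to reference 8. The section concludes from uptake alone that these patients qualify for therapy, and then that "between 12 to 36 patients will be enrolled in the selection part in order to ensure the necessary sample size for the therapeutic part".
- **Abstract, Methods.** Thirty-six is the upper limit of enrolment into the selection part.
- **Study design.** Entry to the therapeutic part needs at least one lesion with uptake and is also conditional on dosimetry: "if mean absorbed dose (AD) to liver < 26 Gy, kidney AD < 16.2 Gy, lung AD < 15 Gy", with a retina limit of 40 Gy. The Abstract and the Selection part under Study procedures repeat that both conditions apply.
- **Personalized dosimetry.** The time-integrated activity from the diagnostic injection "is then scaled with the expected injected activity for therapeutic part", and the less favourable of the 2D and 3D results is kept.
- **Discussion.** "BZA2 phase 3 studies showed that approximately 50% of metastatic lesions did not capture melanin radiotracer", cited to reference 17.

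**The concern.** Two features of the calculation make the claimed assurance too strong.

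First, the trial has two conditions for therapy and the calculation uses one. Treating uptake as eligibility assumes that every patient with an avid lesion meets all four organ limits.

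Second, dividing the target by the rate gives the enrolment at which the target is met on average. That is about an even chance of falling short, not an assurance.

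At stake is whether the enrolment cap can supply the upper part of the planned therapeutic sample, should dose finding need it.

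A third, separate matter is the source of the 50%. The same phase III work is reported per patient in Sample size and per lesion in the Discussion, under different references. The Background cites reference 17 for the phase III study and uses reference 8 for non-response and resistance to systemic treatment. The one input that drives the selection-part size therefore cannot be traced unambiguously within the article.

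**Working it through.** **Inputs from the article:** 6 (minimum) and 18 (maximum) treated; uptake rate 0.50; enrolment 12 to 36, with 36 as the cap; eligibility equal to uptake plus four organ limits.

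**Inputs not in the article (assumed):** the share q of patients with uptake who meet all four limits, and the number k of lesions per patient.

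**Step 1: reproduce the plan's figures.** N = treated / rate. 6/0.5 = 12 and 18/0.5 = 36. Both match exactly, so no dosimetry loss and no margin was built in.

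**Step 2: probability of 18 eligible at the plan's own rate.** Let X be the number eligible among 36, binomial with probability p. Then P(X ≥ 18) = Σ C(36,x) pˣ (1−p)³⁶⁻ˣ, summed from x = 18 to 36. At p = 0.5 symmetry gives a check by hand: 0.5 + 0.5 × C(36,18)/2³⁶ = 0.5 + 0.5 × 0.132 = 0.566.

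**Step 3: add the second condition.** p = 0.5 × q.

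| Assumed q | p | Expected eligible of 36 | P(at least 18 of 36) |
|---|---|---|---|
| 1.0 (as the plan implies) | 0.50 | 18.0 | 0.566 |
| 0.9 | 0.45 | 16.2 | 0.330 |
| 0.8 | 0.40 | 14.4 | 0.146 |

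**Step 4: both ends of the range, over a span of overall eligibility, with 36 enrolled.**

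| Overall eligibility p | P(at least 6) | P(at least 18) |
|---|---|---|
| 0.30 | 0.978 | 0.009 |
| 0.35 | 0.996 | 0.046 |
| 0.40 | 0.999 | 0.146 |
| 0.45 | >0.999 | 0.330 |
| 0.50 | >0.999 | 0.566 |
| 0.60 | >0.999 | 0.917 |

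For 36 enrolled to give 18 eligible with probability 80% or 90%, overall eligibility would have to be about 0.556 or 0.591. Conversely, at p = 0.50 those probabilities need 41 or 44 enrolled.

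**Step 5: direction of the per-lesion reading.** Suppose each lesion has a 50% chance of uptake and a patient has k lesions. If lesions within a patient behave independently, the chance of at least one avid lesion is 1 − 0.5ᵏ, which is 0.75 for k = 2. If they behave identically it stays at 0.50. The patient-level uptake rate then lies between these values, at or above the 50% used. At p = 0.75, before any dosimetry loss, P(at least 18 of 36) is above 0.999.

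**The case against.** The strongest reply is that 18 is a ceiling, not a requirement. The therapeutic part is planned as 6 to 18, and a CRM that stops with fewer than 18 treated has not failed. With 36 enrolled the minimum is practically certain, and intermediate totals are likely: P(at least 12) is 0.986 at p = 0.50 and 0.838 at p = 0.40. This stands, and it confines the point to the upper end of the range. It does not rescue the wording, because the section claims assurance for the whole range and obtained 36 from 18.

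Several stronger readings are tempting, and the document does not support them.

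- *The 50% is really a per-lesion figure, so enrolment is too small.* The article states it both ways and the sources are not at hand, so neither reading can be preferred. Under Step 5 a per-lesion origin would make 36 more adequate, not less.
- *Twelve enrolled will often give fewer than 6 treated.* Twelve is the lower end of a range. Nothing stops enrolment there.
- *The organ limits will remove patients at the higher activity levels.* Linear scaling means that a higher level cannot pass more patients than a lower one. Whether it passes fewer is unknown. The lung dose quoted in the Background belongs to a different compound, and converting it to MBq/m² would need an assumed body surface area, so it says nothing reliable here.
- *Eligibility is settled before the level is known.* The article does say "After verification of the eligibity criteria for therapeutic part, a dose allocation request will be done using an eCRF". But the dosimetry is already scaled to an expected activity, and the request may simply be the formal assignment. A condensed article does not establish an error of sequence.

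**Conclusion.** The point holds in limited form. The calculation omits an eligibility condition that the article itself imposes, and it plans to the mean, so 36 enrolled do not ensure 18 treated. The probability is 0.57 at the plan's own 50%. It is 0.33 or 0.15 if 90% or 80% of patients with uptake meet the organ limits. The minimum of 6 is secure from 36 enrolled, with probability above 0.99 for eligibility of 35% or more.

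The 0.57 rests only on the article's rate, independence between patients and every eligible patient being treated. The lower figures also rest on assumed dosimetry pass rates, which the article does not give. A reader might infer that the dose finding itself is compromised. The document does not show that, since the number of patients the CRM will need is not fixed at 18.

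The per-patient and per-lesion statements of the BZA2 result, and their two references, contradict each other as written and must be reconciled. That is a separate correction, not evidence of a shortfall.

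**What to change.** In Sample size:

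1. State one sourced patient-level eligibility rate that covers both uptake and the four organ limits at the allocated level. If no source exists for the dosimetry part, say that it is assumed and give a range.
2. Replace the assurance with the probability of reaching 6 and 18 treated from up to 36 enrolled, over a range of eligibility. For 30% to 60%, P(at least 18) runs from 0.01 to 0.92 and P(at least 6) from 0.98 to nearly 1.
3. Reconcile the phase III figure between Sample size and Discussion (unit and reference), and use the patient-level value in the calculation.

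The cost is a few sentences and one small table. No extra patients, procedures or design changes are required, though the stated claim becomes less favourable. If the sponsor prefers to keep a firm commitment to 18, enrolment must be sized to a stated probability, for example 44 for 90% at exactly 50% eligibility, and more if dosimetry excludes anyone.

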#### Data analysis

Due to the nature and the design of the study, statistical analysis will be mainly descriptive. Two populations will be analyzed: the diagnostic population (all participants who receive the diagnostic dose) and the therapeutic population (all participants who receive the therapeutic dose). The recommended therapeutic dose will be defined as the highest tested dose for which the percentage of DLT in the diagnostic population is lower than 33%. DLT percentage will be calculated for each tested dose. Only therapeutic population will be included in the analysis of DLT and the efficacy analysis. The statistical significance threshold is set at 5%. Statistical analyses will be performed using R software.

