### Objectives and endpoints

#### Main objective

The primary objective is to determine the recommended dose of [^131^I]ICF01012 to use for pigmented melanoma metastases TRT.

The primary endpoint is the recommended therapeutic dose of [^131^I]ICF01012, defined as the higher dose for which the percentage of dose-limiting toxicity (DLT) is lower than 33%. DLT is defined as any grade 3-4 NCI-CT toxicity, except for alopecia, nausea and vomiting or fever, which can be managed by symptomatic treatment. Only toxicities experienced during the 6 weeks following therapeutic dose administration will be considered as DLT.

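### The recommended-dose rule contradicts itself on its denominator: the 33% DLT limit is set in the diagnostic population, but the DLT analysis is restricted to the therapeutic population

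*Protocol article*

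**What the plan says.** Four statements in the protocol article bear on the denominator.

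- **Data analysis, the rule.** The recommended dose is "the highest tested dose for which the percentage of DLT in the diagnostic population is lower than 33"%. The section defines this population as "the diagnostic population (all participants who receive the diagnostic dose"), so it includes patients who never go on to therapy.
- **Data analysis, the next sentence.** "DLT percentage will be calculated for each tested dose".
- **Data analysis, the sentence after that.** "Only therapeutic population will be included in the analysis of DLT and the efficacy analysis". This population is "the therapeutic population (all participants who receive the therapeutic dose").
- **Main objective.** The primary endpoint is "defined as the higher dose for which the percentage of dose-limiting toxicity (DLT) is lower than 33"%, with no population named. The same section adds: "Only toxicities experienced during the 6 weeks following therapeutic dose administration will be considered as DLT".

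For planning, the Sample size section assumes that "50% of patients will have at least an [^131^I]ICF01012 lesion uptake" and are thus eligible for therapy. It plans 12 to 36 patients in the selection part to yield 6 to 18 in the therapeutic part, with at least 6 at the recommended dose.

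**The concern.** A DLT percentage needs a denominator of patients who could have had a DLT at the dose in question. The only sentence that attaches a population to the 33% rule names a group of which about half is planned never to be at risk. The Main objective section does not settle the matter, because it gives the rule without a population.

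The conflict sits in the criterion that turns the data into the trial's single primary result. If the sentence were followed as worded, untreated patients would enter as DLT-free and pull the percentage down. A dose whose DLT rate among treated patients exceeds the limit could then be reported as below it.

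**Working it through.** **1. Is the diagnostic denominator even defined for each dose?** The percentage is to be calculated per tested dose. A patient who receives only the 185 MBq diagnostic injection is assigned to none of the four therapeutic activity levels and, by the DLT window, cannot contribute a DLT. The literal rule therefore has no denominator at a given dose until someone decides which untreated patients to attach to it. The article gives no rule for that.

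**2. The plan's own figure.** Selection size = therapeutic size / share eligible:

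- 6 / 0.50 = 12
- 18 / 0.50 = 36

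Both ends of the stated 12 to 36 are reproduced, so the planned share treated is 50%.

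**3. Dilution under the literal reading.** Rate in the diagnostic population = rate in treated patients × share treated. At a share of 50%:

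- 50% among treated patients reads as 0.50 × 0.50 = 25%.
- The 33% limit corresponds to 0.33 / 0.50 = 66% among treated patients.

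**4. Effect with 6 treated at a dose.** Six is the stated minimum at the recommended dose. Twelve diagnosed patients per dose is an assumption (6 / 0.50), made only to give the literal rule a value.

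| DLTs | Among 6 treated | Among 12 diagnosed |
|---|---|---|
| 1 | 16.7%, passes | 8.3%, passes |
| 2 | 33.3%, fails | 16.7%, passes |
| 3 | 50.0%, fails | 25.0%, passes |
| 4 | 66.7%, fails | 33.3%, fails |

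The check passes with at most 1 DLT under the therapeutic denominator and with at most 3 under the assumed diagnostic one.

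**5. Chance that the final percentage check passes.** With X ~ Binomial(6, p), compare P(X ≤ 1) with P(X ≤ 3). At p = 0.5 these are (1 + 6)/64 = 10.9% and (1 + 6 + 15 + 20)/64 = 65.6%.

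| True DLT rate p | P(X ≤ 1), 6 treated | P(X ≤ 3), 12 diagnosed |
|---|---|---|
| 33% | 35.8% | 90.3% |
| 50% | 10.9% | 65.6% |
| 60% | 4.1% | 45.6% |

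**6. Sensitivity to the assumed share treated, with 6 treated.**

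| Share treated | Diagnosed per dose | 50% among treated reads as | Most DLTs that pass | Pass probability at p = 0.5 |
|---|---|---|---|---|
| 40% | 6 / 0.40 = 15 | 20% | 4 | 89.1% |
| 50% | 6 / 0.50 = 12 | 25% | 3 | 65.6% |
| 60% | 6 / 0.60 = 10 | 30% | 3 | 65.6% |
| 75% | 6 / 0.75 = 8 | 37.5% | 2 | 34.4% |

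The break-even is 0.33 / 0.50 = 66%. Above that share, a 50% DLT rate is no longer diluted below the limit. In the other direction, the planned 50% rests on lesion uptake alone, while the Study design section also requires acceptable absorbed doses to four organs. The share actually treated could therefore fall below 50%.

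**The case against.** The strongest reply is that this is a slip of wording and that the intended reading can be recovered from the same paragraph. The DLT analysis is restricted to the therapeutic population, the percentage is taken per tested dose, and the DLT window starts at the therapeutic injection. A rule that cannot be computed as worded is unlikely to be run as worded. Someone would probably notice and use the treated patients. This largely stands, and it is why the point is a contradiction to be resolved rather than a wrong analysis already fixed.

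It follows that two stronger readings are not supported.

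- A reader might infer that the rule in force halves the DLT rate and that the trial will accept a dose with 50% toxicity. The article does not consistently fix the diagnostic denominator, so this describes only one side of the conflict.
- A reader might also divide the DLTs at one dose by all 36 selection patients, so that even 6 DLTs in 6 treated patients would read as 6/36 = 16.7%. Nothing in the article suggests pooling patients diagnosed for all doses against a single dose. It would also take six DLTs in six patients at one level, under CRM-driven escalation and with a monitoring committee that meets at each observed DLT.

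It is also fair to say that the binomial figures treat six patients at a dose as a fixed sample. Under a CRM the number at a dose depends on earlier outcomes. The figures describe the closing percentage check only and are not the trial's probability of recommending a toxic dose.

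What does not stand is that the matter can be left alone. The CRM governs escalation, and the monitoring committee advises on continuing, modifying or stopping. Neither corrects the denominator of the percentage by which the result is declared. Nor is this a detail that an article leaves to a fuller document: the article names a population, and it is the wrong one.

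**Conclusion.** The contradiction is certain and lies in the decision rule for the primary endpoint. By the article's own DLT definition the diagnostic population is the wrong denominator, and the later sentence in the same section points to the right one.

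The numerical size is conditional. It requires a literal reading, six treated patients at the dose, and an assumed attachment of untreated patients to that dose at the planned 50% share. On those terms the DLT rate is halved, and 2 or 3 DLTs in 6 change from fail to pass. At other shares the effect is larger or smaller, as shown above. The documents do not show that the diagnostic denominator will actually be used, so the size is what the ambiguity permits and not a forecast.

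**What to change.** In the Data analysis section, replace the reference to the diagnostic population in the recommended-dose sentence by: *among patients of the therapeutic population treated at that dose level*. The rule then agrees with the later sentence in that section and with the DLT window in the Main objective section. Naming the same population in the Main objective section would remove the remaining gap.

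Check that any analysis plan uses the same denominator. It is not shown here, so whether it carries the same wording is unknown.

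The cost is one phrase, and a second if the Main objective section is aligned. No patients, data or design features change. Settle it before the recommended dose is declared.
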